#### Resource utilization

There is little evidence about the economic impacts of pharmacist prescribing. Yet, if BP is reduced in a sustained fashion, this will reduce strokes and other cardiovascular events, which would likely have a significant economic impact. In a systematic review of pharmacist prescribing in the United Kingdom, none of the included studies had an economic component [29]. A retrospective review of supplementary pharmacist prescribing in the United Kingdom showed that between 2004 and 2006, pharmacist prescribing accounted for 0.004% of all prescriptions and 0.003% of prescribing costs [30]. This analysis was limited to prescription costs only; there was no consideration of costs related to pharmacist time, healthcare utilization, or other patient-related costs (*e.g*., travel, home BP monitoring).

The primary objective of this substudy is to evaluate the effect of enhanced pharmacist care on healthcare utilization (hospitalization, emergency room visits, physician visits, use of laboratory testing, use of antihypertensive and other vascular risk-reduction medications). Data will be obtained through Alberta Health Services and Alberta Health and Wellness regarding physician visits and hospitalizations.

### Study organization and management

The study steering committee consists of pharmacists, researchers, a family physician in rural practice, and physicians with expertise in hypertension. The steering committee is involved in study design, education of pharmacists, and liaising with local physician groups and is available for consultation for difficult cases. The study coordination, including randomization, database design, data entry, and project management, is done centrally through COMPRIS/EPICORE Centre, a nonprofit academic research organization http://www.epicore.ualberta.ca.

### Investigator meetings

In April 2009, the first investigator meeting and training session was held. It consisted of a didactic component on the current guidelines for the treatment of hypertension and was followed by small group discussions on patient cases, study procedures, patient assessment, and applying for additional prescribing authorization.

Additional pharmacists were invited to participate in the study, and another investigator meeting was held in September 2010 as an update to pharmacists who were already enrolled and a welcome to the new pharmacists.

An interim meeting will also be held once half the required patients are accrued.

### Site visits

The sites are spread across the province, with the two farthest points being over 1,000 kilometers apart. In order to offer continued and ongoing support to the pharmacists, site visits are scheduled during recruitment. The first wave of site visits was conducted during May 2010, with each site being visited by one or two study team members. Information regarding community-specific recruitment strategies was provided to each pharmacist.

### Ongoing support

In order to maintain pharmacist engagement in the study, the study team offers various methods of support. Firstly, monthly newsletters are sent to all sites as well as study sponsors. The newsletters contain study updates, specifically, enrollment to date; clinical pearls; study form reminders; cases; and summaries of recent research. The newsletter format is short (usually three to four pages), and therefore, additional information is often posted on the study website for pharmacists who want further information. Secondly, the study website includes posted information, notices, and discussion boards where pharmacists can post questions and have their colleagues respond. Finally, teleconferences are scheduled monthly, and all pharmacists are invited to participate. The teleconferences are held on rotating days and in the evening, to help accommodate any other commitments the pharmacists may have. An agenda is circulated prior to the teleconference, along with any additional information that may be discussed (a recent study, patient cases, etc.). The study pharmacists can also submit questions or cases that they would like help with. They present the information to the other pharmacists on the call and discussion ensues. Of all the ongoing support mechanisms in place, the pharmacists use the teleconferences most frequently.

### Study status

To date, one-third of the required sample size has been recruited. There are 15 sites and 17 pharmacists actively screening, recruiting, and following patients.

## Discussion

The study design randomizes patients to enhanced pharmacist care or usual care at the patient level rather than at the pharmacist level. Because of the additional workload inherent in enhanced pharmacist care (including provision of lifestyle counselling, prescribing/titration of antihypertensive medications, and more frequent follow-up) a cluster approach was not seen to be feasible for pharmacists who would have been randomized to enhanced care by this approach. In addition, since all pharmacists involved in the study have additional prescribing authorization, it would not be acceptable for them to be randomized to usual care only. However, the possibility for contamination of the sample is acknowledged. Such contamination may affect the quality of care provided to usual-care patients by each pharmacist and may also affect the pharmacists' responses to the two remuneration schemes since pharmacists will potentially be subject to receiving different payments among their enhanced-care cohort of patients. While contamination may occur, it will bias results towards the null hypothesis; therefore, if a significant difference is found, the result will be more robust.

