### Randomization

After their screening is complete, patients will be invited to participate. Once the patient provides informed written consent, the participant is randomized (via a centralized secure website to ensure allocation concealment) in a 2:1 ratio to either enhanced pharmacist care or usual care (Figure 1) and enrolled by the pharmacist. The patients randomized to the enhanced pharmacist care group are further randomized to one of two payment structures for the pharmacist (fee for visit or payment for performance, Figure 2) in a 1:1 ratio. The randomization strategy employs variable blocked randomization stratified by study center.

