### Sample size and statistical analysis

Based on a two-sample, two-sided *t*-test, a sample size of 162 will provide 80% power to detect a minimally important clinical difference (MCID) of 8 mm Hg between intervention and usual-care groups, with a projected standard deviation of 18 in each group [12]. In the comparison of different payment models within the intervention arm, an alpha of 0.10 was used for a total of 224 patients to detect a 6 mm Hg MCID between the fee-for-visit group and the payment-for-performance group.

Assuming a drop-out or loss to follow-up rate of 10%, the sample size has been increased to 250 in the intervention group (125 in fee for service and 125 in payment for performance) and 90 in the usual-care group, for a total sample size of 340.

All analyses will be intention to treat. A comparison of baseline characteristics will be performed using *t*-tests or nonparametric Wilcoxon for continuous variables and chi-squared test for categorical variables. In order to account for any imbalance in baseline characteristics, the test for differences in change in SBP between intervention and usual-care groups will be adjusted for using multiple regression models (or analysis of covariance models). The problem of missing values will be checked for nonrandomness, and appropriate imputation methods will be applied when needed. All analyses will be carried out using SAS 9.1.3 (SAS Institute, Cary, NC, USA).

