### Substudies

#### Examining the effect of different remuneration models for pharmacists

Current remuneration for community pharmacists in Alberta is based on a per-prescription fee. However, with the advancement of pharmacy services to a patient-centered care model, research into other payment models is a priority. A recent review of remuneration systems for pharmacy services demonstrated a wide variety of models in place, with little analysis of outcomes and sustainability [21].

The objective of this substudy is to evaluate the clinical effect of two pharmacist remuneration models: a payment-for-performance model versus a fee-for-visit model.

Patients randomized into the intervention arm of the study are further randomized in a 1:1 ratio into either payment-for-performance or fee-for-visit remuneration models for the pharmacist. For those patients randomized into the fee-for-visit remuneration model, the pharmacist providing care receives a payment of $150 CDN for the first visit (expected to last approximately 60 minutes) and $75 per visit thereafter (expected to last approximately 20 minutes, plus 10 minutes for documentation), up to a maximum of six visits (Figure 2). For patients randomized into the payment-for-performance remuneration model, the pharmacist providing care receives $150 for the initial visit and $75 for each additional visit as outlined above, and also receives a bonus of $125 if the patient reaches 50% of their target (*i.e*., 50% of the change from baseline needed to reach target) and/or $250 if the patient reaches their target BP for two consecutive visits.

The primary outcome for this substudy is a comparison of SBP reduction achieved between patients in the payment-for-performance remuneration group versus the fee-for-visit remuneration group at six-months follow-up.

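### The claim that contamination biases to the null and makes a significant result more robust does not hold for the payment-model comparison, where the direction of bias is unknown

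*Protocol article*

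**What the plan says.** The Randomization section of the protocol article describes a second randomisation inside the enhanced-care arm: "The patients randomized to the enhanced pharmacist care group are further randomized to one of two payment structures for the pharmacist". Allocation between the two schemes is equal. The strategy is "variable blocked randomization stratified by study center", so both schemes occur within a site. The Study overview says that practitioners cannot be blinded.

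The remuneration substudy pays the same visit fees in both groups. For payment-for-performance patients the pharmacist "receives $150 for the initial visit and $75 for each additional visit as outlined above, and also receives a bonus of $125" for getting halfway to target and/or $250 for reaching target at two consecutive visits. The substudy's primary outcome is SBP reduction at six months.

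The Discussion acknowledges contamination. Besides usual-care patients receiving better care, it says that contamination "may also affect the pharmacists' responses to the two remuneration schemes since pharmacists will potentially be subject to receiving different payments among their enhanced-care cohort". It then concludes, for contamination in general, that "it will bias results towards the null hypothesis; therefore, if a significant difference is found, the result will be more robust". It makes no separate statement for the payment comparison.

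**The concern.** The towards-null argument needs contamination to make the two groups more alike. Leakage of enhanced care to usual-care patients does that. Pharmacists' responses to two concurrent payment schemes need not.

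A pharmacist who knows that some patients carry a bonus tied to blood pressure, and others do not, could respond in two ways. Habits formed with bonus patients may carry over to the rest, which narrows the difference. Or time and attention may go preferentially to bonus patients, which widens it compared with what would be seen if each pharmacist worked under one scheme.

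At stake is how a significant payment result may be read. Under the Discussion's sentence it would count as a conservative estimate. It could instead overstate the difference between adopting one scheme and adopting the other, and nothing in the design says which.

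**Working it through.** **1. The plan's own figure.** The sample size section plans "for a total of 224 patients to detect a 6 mm Hg MCID" at alpha 0.10. SD 18, two-sided testing and 80% power are stated there for the main comparison only; I assume that they carry over.

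n per group = 2 (z₀.₉₅ + z₀.₈₀)² SD² / δ² = 2 × (1.645 + 0.842)² × 18² / 6² = 111.3, rounded up to 112, or 224 in total. The figure reproduces, which supports the assumption. Allowing for 10% loss, 224 / 0.9 = 248.9, or 249, against the planned 250. The sample size is not in dispute.

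**2. What counts as significant.** SE = 18 × √(2/112) = 2.405 mm Hg. The smallest difference significant at two-sided 0.10 is 1.645 × 2.405 = 3.96 mm Hg.

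**3. Two opposite mechanisms.** Let d be the difference that would be seen if each pharmacist worked under one scheme only. Running both schemes side by side changes the expected contrast as follows:
- Spill-over: fee-for-visit patients gain s, so the expected difference is d − s (towards the null).
- Effort shift: bonus patients gain g and fee-for-visit patients lose g, so the expected difference is d + 2g (away from the null when the bonus group is favoured).

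Both need only features in the protocol: patient-level 1:1 allocation within centre, unblinded pharmacists, and a BP-linked bonus on some patients.

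**4. Illustration of size (g is assumed; the documents give no value).** With Δ the expected difference, P(significant) = [1 − Φ(1.645 − Δ/SE)] + Φ(−1.645 − Δ/SE). Take d = 0, so Δ = 2g:

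| g each way (mm Hg) | Δ (mm Hg) | Δ/SE | P(significant) |
|---|---|---|---|
| 0 | 0 | 0 | 10% |
| 0.5 | 1 | 0.416 | 13% |
| 1 | 2 | 0.831 | 21% |
| 1.5 | 3 | 1.247 | 35% |
| 3 | 6 | 2.494 | 80% |

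A shift of 3.96 / 2 = 1.98 mm Hg each way would put the expected difference at the significance threshold.

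**5. Both directions from one starting point.** Take d = 3 mm Hg, for which P(significant) is 35%. Spill-over of s = 3 brings Δ to 0 and P to 10%. An effort shift of g = 1.5 brings Δ to 6 and P to 80%. The sign of the bias depends on which mechanism dominates, and the protocol does not determine that.

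**The case against.** Several points on the other side have weight.

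- **The sentence is a closing remark on limitations.** Neither the analysis section nor the substudy section uses it to decide anything. That is true, but it still tells the reader how to take a significant result, and it follows directly on the statement that "pharmacists will potentially be subject to receiving different payments among their enhanced-care cohort of patients".
- **Effort shifting is undocumented.** All enhanced-care patients have the same follow-up schedule and attract the same visit fees. Planned load is modest: 250 / 17 is about 15 enhanced-care patients per pharmacist, or about 7 per scheme. Spill-over could well dominate. This stands. A reader might infer that the payment result will be inflated, and the documents do not support that. They support only that the direction is open.
- **The percentages are not type I error rates.** A reader might take the 35% as a false-positive rate. It is the power at an assumed 3 mm Hg difference. If patients fare differently because some carry a bonus, that is a real effect of the payment randomised within pharmacists, and the test is valid for that contrast. The result misleads only if read as the effect of adopting either scheme alone.
- **Unequal pay and lost power.** A reader might also object that the schemes differ in total pay, or that power should be restated under contamination. The substudy describes fee plus bonus openly and never claims equal pay. No dilution figure is given, and acknowledging contamination without adjusting for it is a design choice. Neither is an error.

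**Conclusion.** The statement is wrong as written for the payment comparison and defensible for enhanced versus usual care. In the payment comparison the bias may go either way, so a significant difference cannot be called more robust on this ground.

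Its size cannot be derived from the documents. The range of about 13% to 80% for shifts of 0.5 to 3 mm Hg each way rests on an assumed symmetric shift, no difference between the schemes when each is used alone, 112 per group, and SD 18, two-sided testing and 80% power carried over from the main comparison.

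Patient-level randomisation, the sample size and the primary analysis are unaffected. The fault lies in the stated inference.

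**What to change.** In the Discussion:

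- Restrict the towards-null and more-robust statement to leakage of enhanced care in the enhanced versus usual care comparison.
- State that bias in the payment comparison may go in either direction, and why.
- Interpret the payment result as the within-pharmacist effect of adding an outcome bonus for some patients on top of the same visit fees. Do not present it as a conservative estimate of adopting either scheme alone.

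Medication starts and changes, already secondary outcomes, may be tabulated by payment group as description. They should not be offered as a test for effort shifting, because no pharmacist works under one scheme only, and a difference could equally be a genuine response to the incentive. Visit counts are less suitable still, since visit frequency depends on reaching target.

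The cost is a few sentences and an optional table. The downside is a narrower payment conclusion.
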